### 2.3. Design, Randomization, and Blinding

The study will use a between-subject, randomized, double-blind, and sham-controlled design.

The screen for clinical eligibility will be completed on Day 0 of the trial, before the stratified randomization. Randomization occurs immediately after a participant completes the screening assessment, ensuring concealment of allocation. Participants will be allocated randomly to the following conditions: (1) Frontal Group (active tRNS over bilateral dlPFCs + cognitive training); (2) Parietal Group (active tRNS over bilateral PPCs + cognitive training); and (3) Sham Group (Sham tRNS over bilateral dlPFCs/PPCs + cognitive training). An independent researcher will perform the stratified randomization. The stratified randomization will use the minimal sufficient balancing method to prevent imbalances in baseline and will be based on the participants’ demographics (e.g., age, IQ, gender) and MTq [70].

The investigators who assess the participants will be blinded to the allocation, as will the participants and their parents. An independent researcher will maintain the randomization information until the data collection is completed. An emergency code break envelope will be provided to the principal investigator and will only be opened in the case of an emergency, such as a serious adverse event that requires knowledge of the interventions to manage the participant’s condition.

A baseline assessment (see Figure 1) will be completed on Day 1 (T0), before the interventions are administered. Participants will undergo combined interventions for 10 days (5 consecutive days per week for 2 consecutive weeks: from Day 1 to Day 5 and from Day 8 to Day 12). To minimize the influence of intracircadian variations, participants will attend stimulation sessions each day at the same time. Participants will also complete an assessment at the end of the interventions (Day 12, T1), 1 week later (Day 19, T2), and 3 months later (Day 102, T3). At the last follow-up, after the assessment, participants will be asked to guess their stimulation condition by the principal investigator.

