#### 2.5.6. Safety and Tolerability

Symptoms and side effects will be assessed using a standard questionnaire [89] to be completed by participants after each session and at each follow-up (T1, T2, and T3). The questionnaire lists adverse effects, such as headache, neck pain, scalp pain, tingling, itching, burning sensation, skin redness, sleepiness, trouble concentrating, and acute mood change. Participants will quantify the intensity of the symptoms or side effects that are related to tRNS as follows: (1) absent; (2) mild; (3) moderate; and (4) severe.

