### 2.7. Safety Considerations

There are minimal risks that are associated with participation in the study. The potential risks are as follows: (1)Transcranial random noise stimulation. Considering the paucity of safety data on tRNS, this technique is considered safe, as supported by a recent study in juvenile mice [61]. Previous studies [90,91] have shown that tRNS with the current intensity that we use here is less likely to be perceivable. Compared with tDCS, tRNS has the advantage of having higher cutaneous perception thresholds and lower response rates [90]. Adverse effects will be registered throughout the study. The experimenter will also follow participants for adverse effects after the end of the study.(2)Cognitive training/assessment. There is a risk that participants will find the tasks to be challenging, fatiguing, or boring. Should this occur, participants can take a break at any time or can discontinue the testing. Research staff will explain what to do and how to perform the tasks during study visits.

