### 3.2. Statistical Analysis

The Shapiro–Wilk test will be used to test the normality of the data, and Levene’s test will be performed to analyze the homogeneity of the variances. When the data are normally distributed and the assumption of homogeneity is not violated, parametric analyses will be computed. When one assumption is not met, nonparametric tests will be conducted or log-transformation of the distribution will be applied, if appropriate. When appropriate, sphericity will be verified by Mauchly’s sphericity test. When sphericity is not met, Greenhouse–Geisser correction will be applied.

Chi-square analysis will be used to compare groups with regard to demographics, blindness, and safety measures (categorical variables).

Linear mixed-effects models, which account for within-subject correlations more optimally than analysis of variance and automatically handle missing values, allowing maximum use of available data [93], will be run to compare groups for primary (continuous variables: number line subtest) and secondary outcomes (continuous variables: arithmetic, neuropsychological, and psychological measures). The R package lme4 v1.1–17 [94,95], which estimates model parameters using restricted maximum likelihood estimation and computed *p*-values per Satterthwaite’s method [96], will be used. The linear mixed-effects models will include Group (Frontal, Parietal, and Sham) and Time (T0, T1, T2, T3) as fixed factors and Participants as the random factor. Baseline performance will be included as a covariate in our model, because it allows us to make better adjustments for minor differences in pretreatment means. The same analysis will be performed for the training accuracy data, including Group (Frontal, Parietal, and Sham) and Day (from 1 to 10) as fixed factors and participants as the random factor.

Pearson’s correlation will be used to determine whether and the extent to which arithmetic improvements are related to changes in neuropsychological measures, psychological measures, and spectral power of EEG frequency bands at T1, T2, and T3 (from T0).

The statistical results will be corrected for multiple comparisons by Bonferroni’s correction where appropriate.

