### 3.3. Hypothesis and Expected Results

We expect to observe the following:(1)The Parietal, Frontal, and Sham groups will not differ in blindness or safety measures;(2)The Parietal and Frontal groups will experience significant improvements in the primary outcome (Number Line subtest accuracy) and arithmetic and neuropsychological measures at T1 compared with Sham group and that such improvements will persist at T3. The Parietal and Frontal groups will also significantly improve their training accuracy across the 10 days versus the Sham group. We do not have a directional hypothesis on the differences between the 2 active groups (Parietal and Frontal);(3)The Parietal and Frontal groups will significantly improve their psychological measures at least at T3 compared with the Sham group;(4)In the Parietal and Frontal Groups, arithmetic changes will correlate strongly and positively with changes in neuropsychological and spectral power EEG measures at least at T1 and with changes in psychological measures at least at T3.

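### Chi-square is the only test named for side-effect grades that are ordered and repeated up to 13 times per child: pooling sessions would inflate false positives, and one record per child would lose power.

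*Protocol article*

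**What the plan says.** Section 3.2 (Statistical Analysis) gives one method for safety: "Chi-square analysis will be used to compare groups with regard to demographics, blindness, and safety measures (categorical variables"). Section 2.5.6 (Safety and Tolerability) says that the symptom questionnaire is "to be completed by participants after each session and at each follow-up (T1, T2, and T3"), and that each symptom is graded "1) absent; (2) mild; (3) moderate; and (4) severe". The symptoms given as examples are "headache, neck pain, scalp pain, tingling, itching, burning sensation, skin redness, sleepiness, trouble concentrating, and acute mood change", ten in all. Section 2.3 sets the number of sessions: "Participants will undergo combined interventions for 10 days". Section 3.3 states the hypothesis that the comparison serves: "The Parietal, Frontal, and Sham groups will not differ in blindness or safety measures".

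The mixed model with a participant random effect in section 3.2 is assigned to the primary and secondary outcomes and to training accuracy over the ten days. It is not assigned to safety. The nonparametric fallback in the same section depends on checks of normality and equal variance, so it does not clearly reach categorical ratings.

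**The concern.** The safety data have two features that an ordinary chi-square test does not use. The ratings of one child are related to each other, and the grades have an order. Pearson's test assumes independent observations and treats severe, moderate, mild and absent as interchangeable labels.

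The article fixes the test but not the unit of analysis, so the consequence depends on how the table is built. Entering every session as a separate observation would produce false safety signals. Entering one record per child would keep the false-positive rate under control but reduce the chance of seeing a real shift towards worse grades.

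The second consequence matters because of the direction of the hypothesis. Long-term safety of repeated sessions is the first research objective (section 1.3), and section 3.3 expects no difference between groups. A test that misses differences therefore tends to confirm what is expected.

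**Working it through.** **Inputs from the article.** Three arms with 34 per arm recruited, or 26 per arm after the assumed dropout (section 2.6); 10 sessions (section 2.3); ratings after each session and at T1, T2 and T3; four ordered grades (section 2.5.6). The article gives no size, power or error rate for the safety comparison, so there is no plan figure to reproduce. Its 78 participants refer to the repeated-measures ANOVA.

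**Assumptions.** The article gives no symptom rates and no within-child correlation. The grade distributions tried (absent/mild/moderate/severe) were 95/4/0.8/0.2%, 85/11/3/1% and 60/28/10/2%.

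**Number of ratings.** 10 + 3 = 13 per symptom and child. T1 is on Day 12, which is also the last session day, so there are 12 distinct days.

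**Route 1: all sessions in one table.** Take symptom present or absent, three arms and m = 10 sessions. Within-child correlation ρ inflates the variance by D = 1 + (m − 1)ρ. The test has 2 degrees of freedom, so the true rejection rate under no difference is about 0.05^(1/D).

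| ρ | D | 0.05^(1/D) | Simulated (4,000 trials, symptom rates 5-30%) |
|---|---|---|---|
| 0.1 | 1.9 | 0.21 | 0.20-0.21 |
| 0.3 | 3.7 | 0.45 | 0.44-0.45 |
| 0.5 | 5.5 | 0.58 | 0.56-0.60 |

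A second simulation kept all four grades and all 13 ratings, with correlation 0.3 to 0.7 on an underlying normal scale. It gave 17-56% for the rarest distribution and 39-81% for the commonest. With zero correlation it gave 4-6%, so the inflation comes from the dependence.

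**Route 2: one record per child.** Simulated false-positive rates at nominal 5%, 34 per arm:
- one occasion, four grades: 2-4%;
- worst grade per child: 3-6%;
- any symptom versus none: about 5-6% in most settings, lower when nearly every child has the symptom.

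Small counts do arise under these assumptions. An expected count of 5 needs a grade frequency of 5/34 = 14.7%, or 5/26 = 19.2% with 26 per arm. On a single occasion, about 99-100% of simulated tables had more than a fifth of cells below 5. The effect was to make the test conservative.

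**Power on route 2.** Both active arms were shifted by 0.6 SD on the underlying scale, with 34 per arm and within-child correlation 0.5. The rank test uses the same three groups.

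| Record per child | Chi-square | Rank test |
|---|---|---|
| One occasion | about 10-38% | about 23-59% |
| Worst grade | about 50-63% | about 72-81% |

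The ranges run across the grade distributions. A repeat with exactly 10 ratings per child gave 46-65% against 69-82% for worst grade, so these figures should be read to within about 4 points.

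**What a non-significant result would show.** For 10% versus 30% with a symptom in two arms of 34, the standard error is √(2 × 0.2 × 0.8/34) = 0.0970 under no difference and √((0.09 + 0.21)/34) = 0.0939 under the alternative. Then z = (0.20 − 1.96 × 0.0970)/0.0939 ≈ 0.10, which is power of about 54%. Even a threefold rate would be missed almost half the time.

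**The case against.** The strongest reply is that the article never says repeated ratings go into one table. The same sentence covers demographics and blinding, which are recorded once per child, and the authors handle within-child correlation properly for continuous outcomes. A chi-square on one summary per child is a natural reading and a valid test. The choice of summary, and whether an exact version is used, could sit in a full protocol or analysis plan.

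Most of this stands. A reader might infer that the safety comparison has invalid error rates. The article does not support that: inflation follows only if sessions are pooled, and on the other readings the rate is about 2-6%. A reader might also take sparse data as given. Section 2.7 says only that "tRNS with the current intensity that we use here is less likely to be perceivable", which is qualitative, and no event rate appears. Nor do the calculations show that the test is almost blind to real differences: power is reduced, but on worst grade it is still about 50-63% in the scenario tried. That scenario does not isolate moderate or severe grades.

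The reply does not remove the point. Naming chi-square for an ordered scale is a choice stated in the article, and on every unpooled reading it gives up power that an ordinal test would keep. That loss falls on a comparison where the authors expect to find nothing.

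**Conclusion.** The concern holds in a conditional form. Chi-square suits these ratings poorly on either reading. Pooled over 10 sessions, the nominal 5% test would reject in about 20-60% of null trials for within-child correlations of 0.1-0.5. With one record per child the error rate is near nominal or conservative, and the cost is power: about 13 to 21 percentage points on one occasion and 18 to 22 on worst grade, comparing the ends of the ranges above. The sizes rest on assumed grade distributions, correlations and a 0.6 SD shift. The direction rests only on the ordered, repeated structure set out in section 2.5.6.

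Safety is not the primary outcome and does not drive the sample size. The change is still worth making, because safety is the first research objective and hypothesis 1 would be supported by a null result.

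**What to change.** In section 3.2, keep chi-square for categorical demographics and for blinding, and replace it for the safety ratings:

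- For each symptom, reduce the ratings to one value per child: the worst grade over the 10 sessions and, separately, the worst grade over T1 to T3.
- Compare each active arm with Sham by an exact or permutation ordinal test.
- Report, by arm, the proportion of children with at least moderate severity with exact confidence intervals, and do not read non-significance as evidence of equal safety.

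The cost is wording only, since all the ratings are already collected. Session-by-session timing would be described rather than tested. Worst grade does not separate one bad session from ten, and it depends on how many sessions were attended, so the number of ratings per child should be shown by arm. If timing is to be tested, a cumulative-logit mixed model with a child random effect is the alternative.

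### The primary mixed model uses the T0 score both as a response and as the baseline covariate, so it does not deliver the baseline-adjusted T1 and T3 effects that the plan wants

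*Protocol article*

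**What the plan says.** Section 3.2 describes the primary model as containing "Group (Frontal, Parietal, and Sham) and Time (T0, T1, T2, T3) as fixed factors and Participants as the random factor". T0 is therefore a level of the response. The same paragraph adds "Baseline performance will be included as a covariate in our model", giving adjustment for small pretreatment differences as the reason. Section 2.3 fixes what baseline means: "A baseline assessment (see Figure 1) will be completed on Day 1 (T0), before the interventions are administered". The fit is by restricted maximum likelihood with Satterthwaite p-values.

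The hypotheses in section 3.3 are specific to occasions. The active groups are expected to improve on the primary outcome "at T1 compared with Sham group and that such improvements will persist at T3". Section 2.6 derives 78 participants (26 per group) from a repeated-measures ANOVA with 3 groups and 4 measurements at f = 0.15, and plans to recruit 102.

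Section 3.2 neither lists a Group x Time term nor rules one out. It also does not say which coefficient or contrast will be read as the treatment effect.

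**The concern.** A baseline score can be used in two sound ways: as a covariate for the later scores, or as the first response in the series. Using it as both in one model makes the T0 rows regress on themselves. Once the covariate is in, those rows carry no treatment information and have no residual spread of their own, yet the model gives them the same slope, random intercept and residual variance as the T1 to T3 rows.

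This is the primary analysis, and the same model is to be used for the arithmetic, neuropsychological and psychological secondary outcomes. Depending on which terms are fitted and which coefficient is read, the trial could report an effect that is too small, a T1 difference with too narrow a confidence interval, or an estimate without the baseline adjustment that section 3.2 asks for.

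**Working it through.** **Inputs.** From section 2.6: 3 groups, 4 measurements, f = 0.15, alpha 0.05, 80% power, N = 78 (26 per group). From section 3.2: the model terms and the estimator. The article gives no SD or correlation, so the following are assumed: unit variance, equal correlation r between any two occasions (r = 0.3, 0.5, 0.7), a random intercept per participant, the same effect d in both active groups and at T1, T2 and T3, and no dropout.

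**Step 1: the plan's own figure.** For the Group x Time test, the noncentrality is f² x N x m / (1 - r). At r = 0.5 and full sphericity this is 0.0225 x 78 x 4 / 0.5 = 14.04, with (3-1)(4-1) = 6 and (78-3)(4-1) = 225 degrees of freedom. Power is 0.801, so N = 78 is reproduced. At the same r the Group main effect would need 273 and the within-factor test 63. Under the assumed pattern f² = d² x (2/9) x (3/16) = d²/24, so f = 0.15 means d = 0.15 x √24 = 0.735 SD.

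**Step 2: reading (a), main effects only.** With complete data the Group coefficient comes from regressing each participant's mean, (T0+T1+T2+T3)/4, on Group and T0. T0 regressed on Group and itself gives a Group coefficient of 0, so the result is (0 + d + d + d)/4 = 0.75d. For d = 0.5 this is 0.375; simulation gave 0.377, 0.371 and 0.378 at r = 0.3, 0.5 and 0.7. The residual shrinks by the same 3/4, and so does the SE: 0.75 x 0.179 = 0.134 at r = 0.5, as simulated. The t ratio is therefore unchanged. Rejection rates were 0.763, 0.784 and 0.888, identical to a T1-T3 main-effects model, and type I error was 4.5 to 5.3%.

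**Step 3: reading (b), Group x Time added and the group difference at T1 read.** At r = 0.5:
- The common slope on T0 averages 1 (at T0) and r (three times): (1 + 3 x 0.5)/4 = 0.625.
- The true variance of T1 adjusted with that slope is 1 + 0.625² - 2 x 0.625 x 0.5 = 0.7656. The SE of the difference is √(0.7656 x 2/26) = 0.243.
- The model's residual variance is 1 - r = 0.5. Its participant-mean variance is (3/4)² x [(1 - r²)/3 + (2/3) x r(1 - r)] = 0.5625 x 0.4167 = 0.2344, so the random-intercept variance is 0.2344 - 0.5/4 = 0.1094. The total is 0.6094 and the SE is √(0.6094 x 2/26) = 0.217.
- The ratio is 0.217/0.243 = 0.89. The T1 estimate itself is not diluted: simulation gave 0.495, 0.499 and 0.512 for a true 0.5.

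**Step 4: reading (c), Group x Time added and the change from T0 read.** The same covariate term appears at T1 and T0 and cancels. The variance is 2(1 - r) = 1.00 at r = 0.5, against 1 - r² = 0.75 with baseline adjustment. The SEs are √(1.00 x 2/26) = 0.277 and √(0.75 x 2/26) = 0.240. At d = 0.735 the simulated power of this contrast is 0.755, against 0.841 for baseline-adjusted analysis at T1. The omnibus interaction test is sound: in 4,000 simulations per setting, null rejection was 4.8, 5.2 and 4.8%, and its power at d = 0.735 and r = 0.5 was 0.805.

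**Simulation summary** (N = 78, 1,500 trials per setting, fixed degrees of freedom as an approximation to Satterthwaite; Monte Carlo standard error near 5% is √(0.05 x 0.95/1500), about 0.6 percentage points):

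| r | (b) model SE / empirical SE | (b) type I error | (c) SE | T0 as covariate only: SE | T0 as covariate only: type I error |
|---|---|---|---|---|---|
| 0.3 | 0.90-0.92 | 7.1% | 0.327 | 0.265 | 4.9% |
| 0.5 | 0.88-0.90 | 8.9% | 0.277 | 0.240 | 5.8% |
| 0.7 | 0.87 | 8.0% | 0.214 | 0.198 | 4.5% |

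**The case against.** The strongest defence is that a condensed article names factors rather than a model formula. Group x Time was probably meant: the T1 and T3 hypotheses need it, and N = 78 is reproduced as the interaction test (at an assumed correlation of 0.5). On that reading the omnibus test is valid and has its planned power, and the covariate is redundant rather than harmful. The false-positive excess arises only if the T1 group difference is read with the model's SE, and the article does not say that it will be.

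Much of this stands. Three stronger readings are tempting and are not supported:
- **That the plan omits the interaction.** This would be inferred from silence, and sections 2.6 and 3.3 point the other way.
- **That the estimate is diluted and its T1 SE is also wrong.** These belong to different models. Without the interaction there is no T1 contrast to have an SE; with it, the T1 estimate is unbiased.
- **That the primary test is invalid or underpowered.** The main-effects test keeps its size and, with complete data, its power, and so does the omnibus interaction test.

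The defence does not remove the double use of T0, which section 3.2 states outright. Adding the interaction leads to reading (b) or (c), and neither gives a baseline-adjusted occasion-specific effect with a correct SE.

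**Conclusion.** The concern holds as a specification error in the primary model, with a consequence that depends on the reading:
- **(a)** Main effects only: the Group estimate is about 25% too small and there is no T1 or T3 estimate. The harm is to the reported effect size, not to the test.
- **(b)** With Group x Time, group difference at T1: unbiased, but with an SE about 8 to 13% too small and type I error of about 7 to 9%.
- **(c)** With Group x Time, omnibus test or T1-minus-T0 contrast: valid, but the stated adjustment does not occur and precision is lost.

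The 25% follows from the algebra for complete data and an effect constant over T1 to T3. The other sizes also rest on compound symmetry and correlations of 0.3 to 0.7, none of which the article gives. They are not claimed for the 30% dropout that section 2.6 allows for. Participants who leave keep their T0 rows, so the dilution in (a) would be expected to grow.

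**What to change.** Use T0 once. Either option works:
- Take T1, T2 and T3 as responses, with Group, Time, Group x Time and the T0 score as a covariate (baseline x Time is optional). In the simulations this gave T1 estimates of 0.49 to 0.51 for a true 0.5, model SEs within 2% of the empirical ones, and type I error of 4.5 to 5.8%.
- Or keep T0 as a response, constrain the group means to be equal at T0, and drop the covariate.

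In either case, write the Group x Time term into section 3.2 and state that the Frontal-Sham and Parietal-Sham contrasts at T1 and T3 are the estimates to be read, so that the model matches sections 2.6 and 3.3. The same wording should govern the secondary outcomes that share this model. The cost is one reworded paragraph and a few lines of code. No new data are needed, and this calculation gives no reason to change N = 78.

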### 2.4. Interventions

#### 2.4.1. Cognitive Training

Vektor Cognition Matters (https://cognitionmatters.org/, accessed on 5 October 2021) [34,71] is a challenging open-source and age-based training software program that is designed to support and improve the learning of math in children and adolescents. Vektor consists of several domain-specific (numerical abilities) and domain-general tasks (working memory, mental rotation, and logical reasoning) that are automatically and equally alternated for 20 min. As an adaptive training program, it is calibrated to each individual’s performance.

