#### 2.5.2. Neuropsychological Measures

N-back [82] is a working memory task that comprises two conditions: visual-spatial and verbal. The visual-spatial condition consists of a series of visual stimuli (black boxes) in a certain location on the screen. After a training phase, participants are required to indicate whether the location of each box is the same as that of the box that immediately preceded it (level: 1-back). When the accuracy becomes greater than or equal to 80%, the evaluator will increase the difficulty of the n-back (for example, advancing from 1-back to 2-back). Similarly, the verbal condition entails listening to a continuous stream of letters. After a training phase, participants are required to decide whether each letter matches the letter that was heard immediately before (level: 1-back). When the accuracy becomes greater than or equal to 80%, the evaluator will increase the difficulty of the n-back (for example, progressing from 1-back to 2-back).

For both conditions, 35 trials with an interval between stimuli of 3.20 s will be presented. The number of correct answers and errors is considered and will be used to calculate the accuracy percentage on each level of n-back. Higher scores indicate better outcomes and will be considered as an improvement.

Geometric Puzzle. This subtest, as part of the NEPSY, Second Edition [83], measures mental rotation abilities in children and adolescents aged 3 to 16 years. A grid that contains several blank geometric figures in the center of the page is shown with a number of black geometric figures at the bottom. Participants are asked to pair two of the black figures to the two blank figures inside of the grid in a maximum of 45 s. First, participants are given instructions for the test and two practice items. Mental rotation abilities are necessary when the same figures inside and outside of the square are not in the same position, one of which has been rotated. The number of correct answers is recorded, and the raw score is converted into a weighted score. Higher scores reflect better outcomes and will be considered as an improvement.

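### Training accuracy is the tested outcome on a program whose difficulty follows the child's performance, so much of any group difference in learning is diverted into level reached

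*Protocol article*

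**What the plan says.** Three statements in the protocol article bear on the training data.

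- Section 2.4.1 (Cognitive Training), on the Vektor software: "As an adaptive training program, it is calibrated to each individual’s performance". It gives no target success rate, step size or frequency of adjustment.
- Section 3.2 (Statistical Analysis): "The same analysis will be performed for the training accuracy data, including Group (Frontal, Parietal, and Sham) and Day (from 1 to 10"), with participant as the random factor.
- Section 3.3 (Hypothesis and Expected Results): "The Parietal and Frontal groups will also significantly improve their training accuracy across the 10 days versus the Sham group".

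No level reached and no difficulty-weighted training score is named.

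For the N-back, section 2.5.2 sets the progression rule: "When the accuracy becomes greater than or equal to 80%, the evaluator will increase the difficulty of the n-back". Correct answers and errors are then "used to calculate the accuracy percentage on each level of n-back", and a higher score counts as improvement. Highest level reached is not named as a score.

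**The concern.** An adaptive program gives a child who improves harder items. Depending on how quickly it does so, the proportion correct is pulled back towards wherever the program aims to keep it, and the improvement is recorded in the level. Sections 2.4.1, 3.2 and 3.3 therefore sit badly together: the outcome in which the hypothesis expects a difference is one that the intervention's own design works to hold steady. A group that learns faster under stimulation could show little more accuracy than sham, and the result could be misread as no effect of stimulation on learning during training. A later analysis plan that carried out the stated analysis faithfully would keep the problem, because the outcome is already named here.

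The N-back raises a different and smaller issue. A child has a 2-back score only after reaching 80% at 1-back, and likewise for higher levels. After treatment starts, the set of children with higher-level scores depends on their performance, which treatment may change. Comparisons at those levels are not protected by randomization. The N-back is one of two neuropsychological measures and feeds hypotheses 2 and 4 in section 3.3.

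**Working it through.** The plan gives no figure on this point to reproduce, so the check is an illustration under stated assumptions.

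**Training: assumptions.** Accuracy follows a logistic curve, P(correct) = 1/(1 + exp(−(ability − difficulty))). Each child starts at 80% correct, so ability − difficulty = ln(0.8/0.2) = 1.386. There are 100 trials a day for 10 days. One group gains 0.5 logits by Day 10 and the other gains 1.5. None of these values is in the article.

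**Fixed difficulty (the benchmark).**
- Gain 0.5: 1/(1 + exp(−1.886)) = 86.8%.
- Gain 1.5: 1/(1 + exp(−2.886)) = 94.7%.
- Gap: 94.7 − 86.8 = 7.9 points.

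**Adaptive difficulty (simulated).** The trial-by-trial rule raises difficulty by 0.2 × step after a correct answer and lowers it by 0.8 × step after an error. It settles where 0.2p = 0.8(1 − p), that is p = 0.80.

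| Assumed rule | Day 10 accuracy, gain 0.5 vs 1.5 | Gap (points) | Share of 7.9 retained |
|---|---|---|---|
| Trial by trial, step 0.5 | 80.1% vs 80.3% | 0.2 | 3% |
| Trial by trial, step 0.2 | 80.3% vs 80.8% | 0.5 | 6% |
| Trial by trial, step 0.05 | 81.2% vs 83.4% | 2.2 | 28% |
| Adjusted once per day, tight | 80.5% vs 82.8% | 2.3 | 29% |
| Once per day, up at 90% or above, down below 70%, step 0.5 | about 84% vs 87% | about 3 | 38% |
| Same, step 0.25 | about 85% vs 90% | about 5 | 63% |
| Trial by trial, step 0.01 (very slow) | 84.0% vs 90.7% | 6.7 | 85% |

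The last column is the gap divided by 7.9.

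A separate simulation shows where the gain goes. It used 200 trials a day, difficulty up 0.05 after a correct answer and down 0.20 after an error. For ability gains of 0, 0.5, 1.0 and 1.5, Day 10 accuracy was 0.801, 0.801, 0.802 and 0.804. Mean difficulty level rose by about 0, 0.45, 1.0 and 1.5.

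**N-back: assumptions.** Ability has mean 1.2 and SD 0.9 logits. The 2-back is 1.5 logits harder than the 1-back. There are 35 trials per level (the article gives 35 trials; per level is assumed), and passing needs 28/35 = 80%. The true gains examined are 0.3 and 0.6 logits.

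- Without treatment, 46% of children reach 2-back.
- If every child could be scored at 2-back, accuracy would rise by 6.4 and 12.8 points. Among the children who reach it, the observed rises are 3.1 and 6.5 points. The retained shares are 3.1/6.4 = 48% and 6.5/12.8 = 51%, so about half of the gain is lost. Reruns agree to within simulation error.
- At 1-back, which every child has, accuracy starts at 73.7% and rises by 4.8 and 8.9 points.

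The 2-back loss arises because improvement lets weaker children into the scored set and so pulls its mean down.

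**The case against.** The strongest reply is that the article does not describe how Vektor adapts. If the level changes rarely or in small steps, accuracy still carries most of the signal: in the table the slow and coarse rules keep between 38% and 85% of the gap. This stands. A reader might infer that accuracy is pinned to a target whatever the child learns, or that a null result is assured. The article supports neither reading, and no power for this test was calculated. What remains is the direction: every adaptive rule tried shrinks the gap.

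A reader might also infer that the N-back has the same fault. It does not. Accuracy is scored at each level, and each level is a fixed difficulty, so gains can show as higher accuracy there, most clearly at 1-back, where nobody is missing. Only the selection at 2-back and above is at issue. How per-level percentages are combined is detail that a condensed article may leave to the full protocol or analysis plan, and it is not criticised here. The mixed model's tolerance of missing values does not clearly solve the selection, because a child who never reaches 2-back at any visit contributes no 2-back data.

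Nor is the Group by Day model faulted for lacking a random Day slope. Day enters as a fixed factor, and with child-specific slopes simulated, the omnibus interaction test had a type I error of about 6%. The issue is separate from adaptive difficulty.

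Finally, the consequence is limited. The primary outcome is the BDE-2 Number Line subtest. Training accuracy is not among the outcome measures in section 2.5, and the bias is towards no difference, so it would not create a false claim of efficacy on that measure.

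**Conclusion.** The training point holds. The article names an adaptive task, tests accuracy on it and predicts a group difference in that accuracy. Following the plan dilutes the effect that it hypothesises. The size rests on an adaptation rule that the article does not give. Against a 7.9-point gap at fixed difficulty, about 0.2 to 2.3 points remain under trial-by-trial or tight daily adaptation, and about 3 to 7 points under slow or coarse adaptation. These figures assume a logistic response, an 80% starting rate and gains of 0.5 versus 1.5 logits. Confidence is medium for that reason.

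The N-back point holds only as a secondary one: group comparisons at 2-back and above are of children selected after randomization, with about half of a 2-back gain lost under the assumed model. The 1-back score is free of this selection.

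The change should be made, but the primary analysis and the sample size do not depend on it.

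**What to change.** 1. In section 3.2, replace training accuracy as the outcome of the Group by Day model with the daily difficulty level reached in Vektor, or with a difficulty-weighted score. Reword the training hypothesis in section 3.3 to match, and report accuracy descriptively only.
2. In section 2.5.2, define for each N-back condition one score that exists for every child at every completed assessment, such as the highest level passed. Report accuracy at 2-back and above as descriptive, with the number of children reaching each level by group and visit.

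The cost is an export of the level log, which an adaptive program can be assumed to hold but which should be confirmed, and two changes of outcome definition with the matching hypothesis text. Results will be less directly comparable with earlier reports based on accuracy. Visits, interventions and sample size stay as they are.
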